#### Pilot Efficacy Outcomes

The secondary objective of the RCT is to conduct a trial comparing the intervention hypertension app with a control group. The main outcome is clinical changes in blood pressure based on self-reported answers in the questionnaires. The remaining patient-reported outcomes and their associated indicators from baseline to 6 months are shown in Table 2. Adherence to hypertension self-care behaviors will be scored using the validated H-SCALE (Hypertension Self-Care Activity Level Effects) [30] and health care self-efficacy will be scored using the validated Health Confidence Score [31]. Similar outcome measures (eg, medication adherence, diet, physical activity) have been used in other studies of hypertension apps and measure hypertension-specific self-efficacy scores [32].

**Table 2 table2:** Efficacy outcomes and indicators.

Outcome, definitions		Indicator
**Clinical assessment**		
	Difference in mean change in blood pressure from baseline to 6 months between groups	Statistically significant difference in mean change in systolic blood pressure measurements (defined as *P*<.05 using a Pearson test)
	Proportion of patients at their recommended blood pressure	Blood pressure measurements compared to standard ranges

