
Despite this desire for better evidence, only a minority of the mHealth apps available in web-based app stores and commonly downloaded by patients have been evaluated in clinical trials, and due to the fast pace of technological development, those that have been evaluated are often outdated by the time trial results are available. Of the top 100 grossing health and fitness apps, researchers found that none had been formally evaluated in clinical studies [22]. Multiple reviews have highlighted the lack of quality research evidence on the efficacy of apps [9,23-25]. mHealth research has several unique challenges contributing to this problem. Chiefly, technology is rapidly progressing and equally rapid techniques for evaluating such technology are needed. Testing must be cost-efficient, given the limited funding for evaluating mHealth interventions compared with pharmacological interventions or medical devices [9]. These constraints limit the evidence base and the incorporation of apps in patient care.

The rapid proliferation of smartphone technology provides untapped potential to improve the efficient conduct of such research. Using internet-enabled devices to perform research can potentially (1) accelerate large-scale enrolment by contacting and screening potential participants who do not frequently interact with the health system through clinics or hospitals and (2) reduce costs and improve participation by allowing frequent and inexpensive data collection directly from participants. With the rapid development of internet-connected and smartphone-connected consumer devices that can collect biometric data, smartphones also have the potential to collect objective, real-time data directly from patients [26].

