### Sample Size

In the feasibility study, at least 80% of the participants in each group who successfully complete the final questionnaire within 1 year of trial start will be considered as the primary feasibility outcome. To estimate a completion rate of 80% in each group within a margin of error of 8% and with a confidence interval of 95%, we estimated a sample size of at least 100 participants in each group, and 200 participants in total is required. With a sample size of 200 participants in total (ie, 100 per group), we will have 80% power to detect a reduction in blood pressure of 8 mm Hg, which is considered a minimally clinically important difference. Assuming an 18 mm Hg standard deviation in systolic blood pressure, to detect an 8 mm Hg difference between groups with a power of 80% and a type I error of 5%, we would ideally require 81 participants in each arm [28]. Accounting for a 20% dropout rate, we aim to enroll 100 participants in each arm. We recognize that the selected app may not result in such a large difference in the systolic blood pressure, but the calculation is to guide our recruitment targets. If a difference in the blood pressure is found, we will be able to inform patients and physicians that this app may have a major impact on clinical outcomes such as heart attack, stroke, and congestive heart failure. 

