### Data Collection

At 1, 3, and 6 months after enrollment into the RCT, Trial My App will send email reminders with a link to follow-up questionnaires to all participants to assess self-reported blood pressure and several patient-reported outcomes. Completing follow-up will be defined as answering the questionnaire within 7 days of receipt of the questionnaire notification via email. To encourage participation and reduce attrition, participants will receive a Can $10 (US $1=Can $1.27) electronic gift card for each completed assessment and an additional Can $10 gift card if they complete all 4 follow-up assessments.

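### The main blood pressure comparison uses only the baseline-to-6-month change, so 1- and 3-month values already collected do not help when the 6-month report is missing

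*Protocol article*

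**What the plan says.** Data Collection in the protocol article sets the schedule: "At 1, 3, and 6 months after enrollment into the RCT, Trial My App will send email reminders with a link to follow-up questionnaires", sent "to all participants to assess self-reported blood pressure and several patient-reported outcomes". Baseline is the fourth time point.

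Pilot Efficacy Outcomes names the main efficacy outcome without a time point: "The main outcome is clinical changes in blood pressure based on self-reported answers in the questionnaires". Table 2 then fixes it, under Clinical assessment, as "Difference in mean change in blood pressure from baseline to 6 months between groups", judged by a significant difference in mean systolic change at the 5% level using a Pearson test. The other outcomes have the same frame: "The remaining patient-reported outcomes and their associated indicators from baseline to 6 months are shown in Table 2". The row on the proportion at recommended blood pressure names no visit of its own.

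Statistical Analysis says that efficacy outcomes will be compared by logistic regression. It mentions no visit, time or repeated-measures term. On losses, Sample Size says: "Accounting for a 20% dropout rate, we aim to enroll 100 participants in each arm". Study Design describes the trial as nonblinded.

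**The concern.** A change from baseline to 6 months can be computed only for someone with a 6-month value. A participant who reports at 1 and 3 months and then stops drops out of the main blood pressure contrast, although two of that person's three follow-up readings are in the database.

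Participants know their arm, so the reasons for stopping may differ between app users and those given a website link, and may be related to how blood pressure was going. A comparison of 6-month responders is exposed to that. The earlier readings are the best information available on those who left, and the stated analysis sets them aside.

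**Working it through.** **1. The plan's own figure.** Inputs from Sample Size: SD 18 mm Hg, difference 8 mm Hg, power 80%, type I error 5% (two-sided assumed).

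n per arm = 2 × (1.960 + 0.842)² × 18² / 8² = 79.5, rounded up to 80. The t-test version gives 80.4, rounded up to 81, which is the stated figure. Inflated for 20% dropout: 80 / 0.8 = 100, and 81 / 0.8 = 101.25, rounded up to 102. The stated 81 reproduces, and 100 per arm is within rounding. The trial is sized for one between-arm comparison with about 80 evaluable per arm.

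**2. Who falls out of the contrast.** 0.20 × 100 = 20 per arm, or 40 of 200. This is an upper bound on what can be recovered, since only those with at least one earlier report have anything to add. The primary feasibility indicator in Table 1 (80% completing in each group) would be met with this much loss.

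**3. What the earlier reports are worth for the 6-month contrast.** The documents give no between-visit correlation, so I take ρ = 0.3, 0.5 and 0.7, equal for every pair of visits, with SD 18 at each visit. I ignore baseline adjustment, and suppose that 80 per arm report at all visits and 20 report only at months 1 and 3.

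- Share of month-6 variance predicted by months 1 and 3: R² = 2ρ² / (1 + ρ)
- Effective n per arm at month 6 = 1 / [(1 − R²)/80 + R²/100]
- Power for 8 mm Hg (normal approximation) = Φ(8 / (18 × √(2/n)) − 1.96)

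| ρ | R² | Effective n per arm | Power |
|---|---|---|---|
| 6-month values only | – | 80 | 80% |
| 0.3 | 0.138 | 82.3 | 81% |
| 0.5 | 0.333 | 85.7 | 83% |
| 0.7 | 0.576 | 90.4 | 85% |

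The gain in precision at month 6 is real but modest.

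**4. If the effect were constant over visits.** With 80 per arm, the SD of the mean of three visits is 18 × √((1 + 2ρ)/3) = 13.1, 14.7 and 16.1 mm Hg. Power for an 8 mm Hg effect averaged over visits is then 97%, 93% and 88%, against 80% at month 6 alone. This is a different estimand and does not replace the 6-month one.

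**5. What the pilot cannot test well.** The SD of a within-person difference between two visits is 18 × √(2(1 − ρ)) = 21.3, 18.0 and 13.9 mm Hg. The smallest change in effect between two visits detectable with 80% power is 2.80 × SD × √(2/80) = 9.4, 8.0 and 6.2 mm Hg. Power to detect a 4 mm Hg fade is 22%, 29% and 44%.

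**The case against.** The strongest case against is that one prespecified 6-month endpoint is a sound choice, that only a journal article is at hand, and that by-visit estimates and missing-data handling often sit in an analysis plan. Efficacy is also a secondary objective of a pilot, and the sample size already allows for the dropout. Much of this stands: 6 months is not an error, and silence about supporting analyses would be no finding. What remains is that the article defines the outcome as a single two-point change and names methods for it. A better use of the same data can be set against that stated choice. Inflating enrolment protects the number of completers, not the comparability of those who remain.

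Stronger readings are tempting and are not supported:

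- **That the trial cannot show an early or fading effect.** The readings will exist in both randomised arms and can be estimated with confidence intervals. What the article lacks is a stated use of them.
- **That the pilot fails its aim of speed by not settling whether 3 months would do.** The Introduction does say that "technology is rapidly progressing and equally rapid techniques for evaluating such technology are needed", but Objectives names feasibility and blood pressure reduction, not time course or shortest adequate follow-up. The Discussion puts varying degrees of app use outside the study's scope. Step 5 also shows that the question would stay largely open.
- **That the 1- and 3-month rounds are wasted.** Table 1 draws on the follow-up questionnaires for outcome acceptability, app use and data completeness, which serve the primary objective.
- **That a null 6-month result would mislead if an early effect had faded.** It would correctly report no sustained benefit.

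**Conclusion.** The point holds as an improvement to the stated analysis, not as a flaw in the choice of 6 months. Up to about 20 per arm would contribute nothing to the main blood pressure contrast even if they had reported earlier. Using their values would raise the effective number at month 6 from 80 to at most about 82 to 90 per arm. That range assumes correlations of 0.3 to 0.7, equal SDs, and that every dropout gave both earlier reports; with fewer early reports the gain is smaller.

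The main benefit is the weaker assumption about missing data. The 6-month estimate would be valid if dropout depended on arm, baseline and the blood pressures already reported. An analysis of 6-month responders needs dropout not to depend on those intermediate values. Neither approach protects against dropout driven by unreported blood pressure.

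**What to change.** Keep 6 months as the main time point. In Table 2 and Statistical Analysis, state that the between-arm difference in mean change in systolic blood pressure at 6 months will be estimated from one repeated-measures model of all values reported at 1, 3 and 6 months, with arm, visit and arm-by-visit terms and adjustment for baseline. Participants with any follow-up report then contribute. This wording would replace the Pearson test and logistic regression for this outcome.

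Report the 1- and 3-month differences from the same model with confidence intervals, labelled as supporting and descriptive. Say that they may inform follow-up length in later app trials, but that this pilot is not powered to test fading or equivalence of the 3- and 6-month effects.

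The cost is analysis wording only. No extra participants, visits or questionnaire items are needed.

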### Statistical Analysis

Descriptive statistical analysis will be performed on the data set using appropriate statistical methods to measure feasibility. Efficacy outcomes will be compared between the intervention and control groups by using logistic regression.

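### The main efficacy outcome, a difference in mean systolic change, is assigned two conflicting tests (a Pearson test and logistic regression), and neither directly estimates the mm Hg difference the trial was sized on

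*Protocol article*

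**What the plan says.** Three places in the protocol article bear on how the main efficacy outcome is analysed.

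- **Table 2, Clinical assessment.** The first outcome is the between-group difference in mean change in blood pressure over 6 months. Its indicator is: "Statistically significant difference in mean change in systolic blood pressure measurements (defined as *P*<.05 using a Pearson test". A second row gives a binary outcome, the proportion of patients at their recommended pressure.
- **Statistical Analysis.** After a sentence on descriptive feasibility statistics, the whole efficacy analysis is: "Efficacy outcomes will be compared between the intervention and control groups by using logistic regression".
- **Sample Size.** The efficacy calculation is for a difference of 8 mm Hg. It reads "Assuming an 18 mm Hg standard deviation in systolic blood pressure", and at 80% power and 5% type I error concludes "we would ideally require 81 participants in each arm". Then: "Accounting for a 20% dropout rate, we aim to enroll 100 participants in each arm".

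Table 2 also defines the self-care (H-SCALE) and self-efficacy (Health Confidence Score) outcomes as differences in mean change. The Statistical Analysis sentence covers these as well. The article names no t-test, analysis of covariance or linear model.

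**The concern.** The outcome is continuous and the quantity of interest is a difference in means. A Pearson test is either a chi-square test, which needs categories, or a correlation test, which returns a coefficient. Logistic regression with blood pressure as the response needs a binary version of it. The two sections therefore name different methods for one outcome, and neither yields the mm Hg difference directly.

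Two things are at stake. The article treats 8 mm Hg as the minimally important difference, and only an estimate in mm Hg with its confidence interval can be set against that figure. Also, the stated power belongs to a comparison of means. If another analysis is run, the power claim may not carry over. In a nonblinded trial, two conflicting named tests also leave room to choose between them after the data are seen.

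**Working it through.** **Inputs from the article.** Difference 8 mm Hg; SD 18 mm Hg, stated for systolic pressure; power 80%; type I error 5% (sidedness not stated, two-sided assumed); 81 evaluable per arm; 20% dropout; 100 enrolled per arm; 1:1 allocation.

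**Step 1: reproduce the stated sample size.** For a two-sample comparison of means,

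n per arm = 2 × (1.960 + 0.842)² × 18² / 8² = 79.5, so 80 by the normal approximation.

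With the t distribution, power is 0.798 at 80 per arm and 0.803 at 81, so 81 is the smallest n that reaches 80%. The stated 81 is reproduced. For dropout, 81 / 0.8 = 101.25, or 102 per arm; the stated 100 is within two participants of this.

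**Step 2: read the Pearson test as a correlation of change with the arm indicator.** Over 2,000 simulated trials of 81 per arm (difference 8, SD 18), the correlation P value equalled the pooled t-test P value to rounding error, and both rejected in 80.7% of runs. No power is lost, but the output is a correlation coefficient.

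**Step 3: if change were dichotomised so that logistic regression could be used.** The article gives no cut and no control-arm proportion, so these are assumptions. Take normal data and let p_c be the control proportion counted as a success. The intervention proportion is then

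p_t = Φ(z(p_c) + 8/18).

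Power at n = 81 per arm is

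Φ{ [(p_t − p_c)√n − 1.96√(2p̄(1 − p̄))] / √(p_c(1 − p_c) + p_t(1 − p_t)) }, with p̄ the mean of the two proportions.

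Example, p_c = 0.40: p_t = Φ(−0.253 + 0.444) = 0.576 and p̄ = 0.488. The numerator is 0.176 × 9 − 1.96 × 0.707 = 0.197, the denominator is 0.696, and power is Φ(0.28) = 0.61.

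| Assumed control proportion | Intervention proportion | Power, 81 per arm |
|---|---|---|
| 10% | 20.1% | 43.6% |
| 20% | 34.6% | 54.9% |
| 30% | 46.8% | 59.6% |
| 40% | 57.6% | 61.1% |
| 50% | 67.2% | 60.3% |
| 60% | 75.7% | 57.4% |
| 70% | 83.4% | 52.1% |
| 80% | 90.1% | 43.5% |

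The maximum is about 61%, at a cut midway between the arm means. A simulated logistic regression at that cut gave 61.9%, against 80.7% for the t-test on the same data. To restore 80% would take about 126 to 146 evaluable per arm for control proportions of 20% to 50%. If all 100 per arm were analysed, dichotomised power would be 63.9% to 70.4% over that range, against 88% for the comparison of means.

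**Step 4: does SD 18 apply to change?** The Sample Size section gives 18 for systolic pressure, while Table 2 analyses change. With equal SDs at both times and baseline-to-6-month correlation r (an assumption), SD of change = 18√(2(1 − r)).

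| r | SD of change | t-test power, 81 per arm |
|---|---|---|
| 0.3 | 21.3 | 66% |
| 0.5 | 18.0 | 80% |
| 0.7 | 13.9 | 95% |

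So even with the test corrected, the 80% holds for change only if r is about 0.5.

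**The case against.** Several points can fairly be made for the plan.

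- **Dichotomising is not stated.** A reader might infer that the trial will have only 55% to 61% power. The documents do not support that as a fact: they give no cut and no control proportion. Logistic regression also suits the second clinical outcome, the proportion at recommended pressure, and the authors may have had only that in mind. A logistic model with arm as the response and change as the predictor would need no cut, though it would not return mm Hg either. This stands. The power loss is a scenario, and of its figures only the ceiling of about 61% at 81 per arm does not depend on the cut.
- **The mean difference can still be reported.** A reader might infer that the trial cannot produce its mm Hg result. That goes too far. Table 2 names the mean difference as the outcome, and the Pearson wording only sets how significance is judged. On the correlation reading, the P value is that of the t-test.
- **The score outcomes have indicators of their own.** Table 2 refers to the mean Health Confidence Score with a 95% CI, so these outcomes do not rest on the logistic sentence alone. That sentence still does not fit them.
- **Efficacy is secondary in a pilot.** The Sample Size section says that the calculation serves to guide recruitment. This limits the consequence, but the conflict remains.

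The article's brevity does not answer the point. It does not leave the method to a fuller document; it names two methods that disagree.

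**Conclusion.** The point holds as an inconsistent and ill-suited specification of the main efficacy analysis. Table 2 and Statistical Analysis name different methods for a continuous outcome, and neither directly estimates the difference on which the 81 per arm rests. That conclusion follows from the text and needs no outside assumption.

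The size is conditional. Reading the Pearson test as a correlation with arm costs no power. Dichotomising for logistic regression would cap power at about 61% with 81 per arm: about 55% to 61% for assumed control proportions of 20% to 60%, and about 44% at 10% or 80%. These figures assume normal data, a difference of 8 mm Hg and SD 18.

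A reader might also infer that the primary feasibility result is compromised. It is not: the completion rate and its margin of error do not depend on the efficacy test. Nor does naming the right test by itself secure 80% power, because the stated SD is for systolic pressure and not for its change.

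**What to change.** 1. **Table 2.** Replace the Pearson test with a linear-model comparison of 6-month systolic pressure between arms, adjusted for baseline (or a two-sample comparison of mean change). Report the difference in mm Hg with its 95% CI.
2. **Statistical Analysis.** State that continuous outcomes (systolic pressure, H-SCALE, Health Confidence Score) are compared by linear regression, and that logistic regression is used only for binary outcomes such as the proportion at recommended blood pressure.
3. **Sample Size.** State that the 80% power refers to a two-sided comparison of means with SD 18, and that it applies to change only if the baseline-to-6-month correlation is about 0.5 (about 66% at 0.3 and 95% at 0.7, with 81 per arm).

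The cost is a few sentences of wording. No further data or participants are needed, and the feasibility analysis is unchanged.

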**Self-management ability**		
	Difference in mean change of self-managing behaviors	H-SCALE^a^ score and statistically significant correlations with blood pressure at 95% CI
	Difference in mean change in feelings of self-efficacy	Frequency distribution and mean of Health Confidence Score at 95% CI
**Patient-reported outcomes**		
	Descriptive analysis of patient-oriented experiences between groups at baseline and 6 months	Agreeability with goal setting, decision making, sharing data, and empowerment statements in questionnaires developed from the advisory board themes (at 95% CI)

^a^H-SCALE: Hypertension Self-Care Activity Level Effects.

### Statistical Analysis

Descriptive statistical analysis will be performed on the data set using appropriate statistical methods to measure feasibility. Efficacy outcomes will be compared between the intervention and control groups by using logistic regression.

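### The main efficacy outcome, a difference in mean systolic BP change, is assigned two conflicting methods, and neither gives the mm Hg difference the trial is sized on

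*Protocol article*

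**What the plan says.** All references are to the protocol article.

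- **Pilot Efficacy Outcomes:** "The main outcome is clinical changes in blood pressure based on self-reported answers in the questionnaires".
- **Table 2, Clinical assessment, first row:** the outcome is "Difference in mean change in blood pressure from baseline to 6 months between groups". The indicator is "Statistically significant difference in mean change in systolic blood pressure measurements", with P<.05 obtained "using a Pearson test".
- **Table 2, Clinical assessment, second row:** a separate, binary outcome, "Proportion of patients at their recommended blood pressure".
- **Table 2, Self-management ability:** the difference in mean change of self-managing behaviours is indicated by the H-SCALE "score and statistically significant correlations with blood pressure at 95% CI". Self-efficacy is indicated by the frequency distribution and mean of the Health Confidence Score.
- **Statistical Analysis:** "Efficacy outcomes will be compared between the intervention and control groups by using logistic regression". No other method for comparing efficacy between arms is named there.
- **Sample Size:** a difference of 8 mm Hg, SD 18 mm Hg, 80% power and 5% type I error give 81 per arm, raised to 100 per arm for 20% dropout.

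**The concern.** The main efficacy outcome is continuous, and so are the changes in the H-SCALE and Health Confidence scores. The article names two methods for the BP outcome in two places. They are different methods, and neither is designed to estimate a difference in means.

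Two things are at stake. First, the secondary objective is whether the app lowers blood pressure, and the Objectives section wants to know whether the reductions are of a size linked to clinical benefit. That needs an estimate in mm Hg with a confidence interval, which neither named method reports. Second, with two incompatible methods on record, the choice between them, or of a third, could be made after the data are seen.

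Table 2 has a smaller related fault. A correlation of H-SCALE with blood pressure is listed as an indicator of a between-group difference, but a correlation between two participant measurements does not compare the arms.

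**Working it through.** **1. Reproduce the plan's sample size.** Inputs from Sample Size: difference 8 mm Hg, SD 18 mm Hg, power 80%, type I error 5%. Sidedness is not stated, so two-sided is assumed.

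- Normal approximation: n per arm = 2 × [18 × (1.960 + 0.842) / 8]² = 79.5, rounded up to 80.
- Two-sample t-test: 80.4, rounded up to 81, which is the stated figure.
- One-sided: 63, which does not match.
- Power by t-test: 0.803 at 81 per arm and 0.798 at 80 per arm. The 80 is what remains of 100 enrolled after 20% dropout.

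The trial is therefore sized on a two-sided comparison of two means. That arithmetic is sound and is not in dispute.

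**2. Set each named method against the outcome.**

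| Method | Outcome type needed | What it returns | Fits a difference in mean change? |
|---|---|---|---|
| Logistic regression (Statistical Analysis) | Binary or ordered categories | Odds ratio | No |
| Pearson chi-square (one reading of Table 2) | Counts in categories | Test of association | No |
| Pearson correlation of change with a 0/1 arm code (other reading) | Continuous | Correlation coefficient; P value identical to the pooled t-test | Valid unadjusted P value, but no mm Hg difference or CI |
| Comparison of means (implied by Sample Size) | Continuous | Mean difference in mm Hg with CI | Yes, but not named as an analysis |

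The article does not say which Pearson test is meant. On either reading it disagrees with Statistical Analysis.

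**3. What dichotomising would cost, if it were done.** This is an illustration, not the stated plan. Assumptions: normal systolic BP, SD 18, true shift 8 mm Hg, 80 analysed per arm, a single cut at 140 mm Hg. The control means are assumed, because the article gives none.

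Proportion at target: control p1 = Φ((140 − m)/18), app p2 = Φ((148 − m)/18), where m is the control mean. Power = Φ[(p2 − p1 − 1.96 × se0)/se1], where se0 is the pooled and se1 the unpooled standard error.

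For m = 145: p1 = Φ(−0.278) = 0.391 and p2 = Φ(0.167) = 0.566, a difference of 0.176; se0 = 0.0790 and se1 = 0.0778. Power = Φ[(0.1756 − 0.1548)/0.0778] = 0.605.

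| Control mean (mm Hg) | At target, control vs app | Power at 80 per arm |
|---|---|---|
| 138 | 54.4% vs 71.1% | 0.588 |
| 142 | 45.6% vs 63.1% | 0.604 |
| 145 | 39.1% vs 56.6% | 0.605 |
| 150 | 28.9% vs 45.6% | 0.588 |
| 155 | 20.2% vs 34.9% | 0.545 |

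The range is roughly 55-61%, against 79.8% for the comparison of means at the same 80 per arm.

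**The case against.** Four points can be made for the plan as it stands.

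- **Power.** A reader might infer that the planned analysis has only about 60% power. The article does not support that. Table 2 lists mean change and the proportion at recommended BP as separate outcomes, and nothing says the first will be dichotomised. If the Pearson test is a correlation with arm, no power is lost relative to the t-test. The illustration also uses one 140 mm Hg cut, whereas Eligibility Criteria sets different systolic and diastolic targets for people with and without diabetes. This objection stands in full.
- **Scope of logistic regression.** A reader might infer that it suits only the proportion at recommended BP. That goes too far: the agreement statements under Patient-reported outcomes could suit a binary or ordinal logistic model, although that row is labelled descriptive and the response scale is not shown.
- **H-SCALE.** A reader might infer that this outcome is judged only by correlation with BP. The indicator includes the score itself, and the Health Confidence Score indicator includes a mean, so Table 2 does not rely on correlation alone.
- **A pilot, condensed into an article.** Efficacy is the secondary objective, feasibility is analysed descriptively, and the BP calculation is described as a guide to recruitment. That lowers the severity. It does not remove the point, because condensing or deferral to an unseen analysis plan can explain missing detail but not two named methods that contradict each other and the outcome.

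**Conclusion.** The conflict is real and lies in what the article states, not in what it omits. One continuous outcome has two incompatible methods, and neither yields the mm Hg difference behind the 81 per arm. The quantity of interest is clear from Table 2; the error is in the methods attached to it.

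The harm is limited. The sample size is unaffected. A loss of power to roughly 55-61% is conditional on BP being dichotomised, and on the assumed normal distribution, single cut and control means. The documents do not show that the trial is underpowered as planned. Because efficacy is secondary and the primary feasibility aim is untouched, this should be fixed but does not threaten the pilot's main purpose.

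**What to change.** Align Statistical Analysis and Table 2:

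- Compare systolic BP, H-SCALE and Health Confidence Score between arms with a linear model and report the mean difference with 95% CI. Adjusting for the baseline value, which is already collected, is preferable. A t-test or linear model on the change would also remove the error.
- Keep logistic regression for the proportion at recommended BP and any other categorical outcome.
- Delete the Pearson test from the systolic BP row.
- Label the H-SCALE/BP correlation as an exploratory association, alongside the between-arm comparison of the score.

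The cost is wording in these two places. No further data or participants are needed, and the 81 per arm stands.
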